### Interim analyses {21b}

We do not have any pre-determined interim analysis and stopping guidelines as our study is low risk, and they are not required by ethics; however, using the facility and strategy tracker, we continuously assess the extent to which our strategies are implemented as planned. If they are not implemented as planned, we work with stakeholders and participants to ensure improved fidelity or adapt such strategies to promote integration of hypertension care into the HIV service platform.

## Methods for additional analyses (e.g., subgroup analyses) {20b}

### Qualitative and mixed methods analyses

We will use directed content analysis methods using the CFIR domains [22, 23]. Two team members will independently read all transcripts to develop an initial list of themes, looking for repetitions. They will then develop a codebook listing each theme accompanied by a detailed description, inclusion/exclusion criteria, and typical examples. Using a qualitative data management program, two coders will mark areas of text corresponding to each theme. They will practice by coding randomly selected transcripts independently and reviewing together. If coder disagreement reveals ambiguity in codes, we will add examples. Training will continue until coders consistently identify and mark each theme. Next, both coders will independently code a randomly selected 15% of transcripts to assess coder consistency, evidenced by Kappas of ≥ . 80 [26]. We will examine distribution of themes, overall, and by participant type. We will share the results with each partner group for feedback.

The qualitative and survey results will then be used to help understand the quantitative results of the implementation and effectiveness outcomes using explanatory mixed methods approach [27].

## Methods in analysis to handle protocol non-adherence and any statistical methods to handle missing data {20c}

### Outcomes

Primary and secondary outcomes will be carefully collected, and missing data on the primary and secondary outcomes will not be imputed, but the missingness mechanisms will be explored and factors associated with missingness would be adjusted for in exploratory analysis.

### Covariates

Missing baseline covariates will be imputed using simple imputation methods in the covariate adjusted analysis based on the covariate distribution, should the missing values for a particular covariate be less than 5%. For a continuous variable, missing values will be imputed from random values from a normal distribution with mean and SD calculated from the available sample. For a categorical variable, missing values will be imputed from random values from a multinomial distribution with probabilities $${P}_{1},{P}_{2},\dots ,{P}_{k}$$ from the sample. For a count data, missing values will be imputed from random values from a Poisson distribution with $$\lambda$$ from the sample. If the missing values for a covariate are > 5%, then they will be imputed using Markov chain Monte Carlo (MCMC) methods using SAS PROC MI.

### Plans to give access to the full protocol, participant-level data, and statistical code {31c}

Data recorded as part of the study will be anonymized and will be deposited in a secured archiving facility at the University of Botswana Health Records Unit and the Botswana Ministry of Health Research Ethics Committee. We will also comply with funder requirements for data sharing. Researchers may request access to the data as part of transparency and data sharing; however, this is strictly upon request and will be governed through the required legal office, with at the least a data sharing agreement in place. The agreement will also detail the requirements and process for requesting access to the full protocol, a deidentified participant-level dataset, and statistical code.

## Oversight and monitoring

### Composition of the coordinating center and trial steering committee {5d}

#### Principal investigators

The principal investigators has the overall responsibility for the design and conduct of the study and preparation of the protocol and subsequent adaptations and revisions, in collaboration with the steering committee and the data safety monitoring board (DSMB).

#### Steering committee

This group, consisting of the principal investigators, study chair, study statistician, involved subject matter experts, and national leaders (representatives of site countries). The committee consists of persons with expertise in implementation science, biostatistics, epidemiology, behavioral science, infectious diseases, and internal medicine, among others. They meet on a regular basis to assess study progress and discuss necessary interventions or protocol amendments as required. Specific responsibilities include the following:Agreement of the final protocol and the statistical analysis planReviewing progress of the study and, if necessary, deciding on protocol changesReview and approval of study publications and sub-study proposalsReviewing new studies that may be of relevanceProviding reports as required by the study DSMB. The DSMB was independently appointed by the study sponsor.

#### Central coordination and study management

The study will be coordinated through University of Botswana, in collaboration as a joint partnership with ACHAP, BHP, Rand Corporation, Northwestern University, LSHTM, University College of London, and WUSTL. Regular meetings are coordinated between a primary team consisting of the principal investigators, central research coordinators, and relevant team members to assess trial progress on an ongoing basis, review recruitment rates by site, and address any potential need for site visits or direct intervention. Specific responsibilities include the following:Study planning and organization of steering committee meetingsEnsuring necessary regulatory and ethics committee approvalsDevelopment of standard operating procedures and computer systemsMonitoring overall progress of the studyProvision of study materials to study sitesMonitoring and reporting safety information in line with the protocol and regulatory requirementsDealing with technical, medical, and administrative queries from study sites

#### Study sites

Participating facilities are represented by investigators, i.e., nurses and research assistants. Each site is led by a nurse supervisor. The investigators perform the study in accordance with Good Clinical Practice (GCP) and every new investigator provide documentation of their qualifications to the project office prior to study start. The investigator is required to ensure compliance with respect to the visit schedule and procedures required by the protocol. The investigator agrees to provide all information requested in the case report forms in an accurate and timely manner according to instructions provided. Random or for cause monitoring visits will be done by project representatives. National leaders and principal investigators are responsible for:Obtaining all relevant local permissions (assisted by the coordinating centers)All trial activities at the local site, including appropriate training and supervision for clinical staffConducting trial procedures at the local site in line with all relevant local policies and proceduresDealing with enquiries from participants and others

### Composition of the data monitoring committee, its role and reporting structure {21a}

An independent DSMB reviews the accumulating study data on yearly basis (the frequency of review can be adjusted at their discretion based on emerging data) and makes recommendations to the study leadership about the conduct of the trial, integrity of the data, and trial discontinuation to ensure the overall safety of participants. The DSMB is provided with summaries of safety (all reportable AEs), efficacy (deaths and hospitalization), and administrative (including accrual, retention, compliance with study requirements) data.

### Adverse event reporting and harms {22}

While this protocol does not involve the administration of any study products, the study team will report in real-time, to IRBs and to the NHLBI applicable policy (https://www.nhlbi.nih.gov/grants-and-training/policies-and-guidelines/nhlbi-adverse-event-and-unanticipated-problem-reporting-policy or subsequent versions), sponsors, any serious adverse events (SAEs) experienced by a participant that in the opinion of the investigator are BOTH unexpected and at least possibly related to the research procedures. Reportable events will be reported within 7 days of the study team becoming aware of the event. The AE reporting period for this study is from the time of enrolment to the end of study follow-up for a participant.

Upon consultation with the Botswana Medicines and Health Products Regulatory Agency (BoMRA) on the pharmacovigilance reporting scope of this implementation science clinical trial, any adverse drug reactions should be reported to BoMRA using its online reporting mechanism accessible from this link: https://www.bomra.co.bw/index.php/services/patient-safety-monitoring.

Reportable events will be documented by the intervention clinic staff who will then report through the BoMRA website. The study team who will then notify the IRBs/HRDC of events that meet the SAE reporting criteria. The incident will be discussed and a written action plan will be devised and implemented within 1 week of the initial report, if needed. Written documentation of all reportable events and event resolution will be retained in the study file. These reports follow a pre-defined format as per the regulatory body. For instance, please see https://www.bomra.co.bw/index.php/suspected-adverse-drug-reactions-reporting-form for BOMRA online form and associated requirements. Reporting of events to IRBs and the study sponsor will follow institutional and IRB policies.

Adverse events (AEs) will be summarized using the number of AEs and the number (%) of participants with AEs by treatment arms. Safety analyses will summarize the number of grade III/IV AEs, graded according to Division of AIDS (DAIDS) criteria; serious adverse events (SAEs); serious adverse reactions (SARs); suspected unexpected serious adverse reactions (SUSARs); and deaths occurring after randomization. We will also measure unintended effects of HTN integration on HIV such as impact on viral suppression rates among participants.

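### The adverse event section gives the documenting of reportable events to intervention clinic staff, yet plans AE summaries by arm, so ascertainment may differ between arms

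*Protocol article*

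**What the plan says.** All of the following is in the protocol article.

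- **Who documents.** Adverse event reporting and harms {22}: "Reportable events will be documented by the intervention clinic staff who will then report through the BoMRA website". Control clinic staff are not mentioned. The study team then notifies the ethics bodies of events that meet the SAE criteria.
- **What is expedited.** The same section has the study team report "any serious adverse events (SAEs) experienced by a participant that in the opinion of the investigator are BOTH unexpected and at least possibly related", meaning related to trial procedures, and says that "any adverse drug reactions should be reported to BoMRA using its online reporting mechanism".
- **For how long.** "The AE reporting period for this study is from the time of enrolment to the end of study follow-up for a participant".
- **What is tabulated.** "Adverse events (AEs) will be summarized using the number of AEs and the number (%) of participants with AEs by treatment arms". Further, "Safety analyses will summarize the number of grade III/IV AEs, graded according to Division of AIDS (DAIDS) criteria", together with SAEs, SARs, SUSARs and deaths.
- **What the DSMB sees.** Composition of the data monitoring committee {21a}: "The DSMB is provided with summaries of safety (all reportable AEs), efficacy (deaths and hospitalization"), plus administrative data.

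**The concern.** A by-arm count of AEs can be read as a safety result only if events are looked for in the same way in both arms. Here the one sentence that says who documents events names staff in one arm.

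The design adds to the asymmetry. Nobody is blinded, and that includes the analysts (Who will be blinded {17a}). Intervention staff receive hypertension training, practice facilitation and monthly audit with feedback (Intervention description {11a}). Their patients also receive booster calls, monthly while blood pressure is uncontrolled (Strategies to improve adherence {11c}). Table 2 expects antihypertensive prescribing of 80% in the intervention arm against 57% under standard of care. Drug exposure, patient contact and the stated reporting duty therefore all lean the same way.

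The DSMB may recommend discontinuation, and Interim analyses {21b} sets no stopping guideline, so it relies on judgement of these summaries. An apparent excess in the intervention arm could come from reporting, and a real excess could be put down to reporting.

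**Working it through.** The article states no AE rate, safety test or safety power, so there is no figure to reproduce. The check has two parts.

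**1. Does any other text assign AE capture in control clinics?**

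| Section | What it provides in both arms | Does it assign AE capture in control clinics? |
|---|---|---|
| Adverse event reporting and harms {22}, SAE duty | Applies to any participant | No. It is a reporting duty that starts once the study team is aware, and it covers only SAEs that are "BOTH unexpected and at least possibly related to the research procedures" |
| Same section, AE period | Enrolment to end of follow-up | No. It sets the time window, not the person or the method |
| Plans for assessment {18a} | Study visits at months 6, 12, 18 and 24 | No. The listed items are socio-demographics, co-morbidities, medication, cardiovascular data and treatment partner sessions |
| Study sites {5d} | Nurses and research assistants as site investigators, completing case report forms | No. They could do it, but the task is not given to them |
| Auditing {23} | Audit of forms and modified EHR records | No. The audit covers partner support, laboratory tests and anthropometry, and control clinics have no EHR modifications |
| Data monitoring {21a} | Deaths and hospitalisation to the DSMB | Not stated how they are found, but a separate item with no arm restriction |

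Several provisions are neutral as to arm. None says who records AEs in a control clinic.

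**2. What would unequal capture do to the table?**

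Inputs: 4652 participants (Sample size {14}). An equal split is assumed, so 4652 / 2 = 2326 per arm. The AE risk p and the share s of control-arm events captured are not in the article and are assumed. Intervention capture is set to 100%, and the true risk is the same in both arms.

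- Intervention participants shown = 2326 × p
- Control participants shown = 2326 × p × s
- Apparent ratio = 1 / s, whatever p is

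With p = 3%, the intervention count is 2326 × 0.03 = 69.8.

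| Control capture s | Control count (69.8 × s) | Apparent ratio |
|---|---|---|
| 100% | 69.8 | 1.0 |
| 80% | 55.8 | 1.25 |
| 50% | 34.9 | 2.0 |
| 20% | 14.0 | 5.0 |
| 0% | 0 | not finite |

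At p = 1% and s = 50% the counts are 23.3 and 11.6. At p = 5% they are 116.3 and 58.2. The ratio is 2.0 each time.

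The table cannot be decoded afterwards. True risks of 3% and 1.5% with full capture in both arms give 69.8 and 2326 × 0.015 = 34.9. That is the same pair of counts as no true difference with half the control events missed.

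**The case against.** The strongest reply is that two streams are being mixed. The sentence on intervention clinic staff follows the text on adverse drug reactions and describes submission to the medicines regulator. The limit to unexpected and possibly related events governs expedited reporting. Neither is stated to be the source of the by-arm table, which covers AEs more widely. The SAE duty, the AE period and the study visits are not restricted by arm. The article condenses a full protocol that may hold the AE forms, and the phrase about intervention clinics may be loose wording for study clinics. The trial gives no study product, and the AE plan is a descriptive summary, not a test.

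Much of this stands. A reader might infer that control-arm harms go unrecorded, that control counts will be near zero by design, or that the safety comparison is already biased. The document supports none of these. It does not say that only intervention staff document events. It leaves possible routes for SAEs and deaths in control clinics, and it sends deaths and hospitalisation to the DSMB as an item separate from reportable AEs. The capture shares used above are assumptions, and the ratios merely restate them.

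The reply does not remove the point. This is not just detail left to a fuller document: the article states an assignment, and that assignment names one arm. The arm-neutral provisions do not fill the gap, because none gives anyone the task of recording AEs in control clinics. And the reportable AEs, which are the events the sentence covers, are what the DSMB receives as its safety summary. If the phrase is loose wording, it still needs correcting.

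**Conclusion.** The point holds as a risk of differential ascertainment. As written, the section names documenters of reportable events in the 7 intervention clinics and none in the 7 control clinics, while planning AE numbers and percentages by arm. Followed literally, this would most likely make the intervention look worse on AEs, and a true excess could not be told apart from fuller reporting.

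The size is unknown. The apparent ratio is 1/s under equal true risk and full intervention capture: 1.25 at 80% control capture and 5.0 at 20%. Nothing in the article says where in that range the trial would fall, or whether capture differs at all in practice. The concern is weaker for deaths and hospitalisations, which may be found by a separate route in both arms. The primary outcomes are not affected.

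**What to change.** 1. Reword Adverse event reporting and harms {22} so that staff at all 14 clinics document reportable events. Keep the route for related and unexpected events as the expedited regulatory route.
2. At the remaining scheduled study visits, record AEs with the same questions in both arms, including grade III/IV events, hospitalisations and deaths, regardless of relatedness. Base the by-arm tables and the DSMB summaries on these data.
3. For visits already past, take deaths and hospitalisations from clinic records in the same way in both arms, and add a caveat on differential ascertainment to the by-arm AE tables.

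Cost: a wording change, an addition to the existing visit form and a few extra minutes per visit. With 4652 participants and four follow-up visits the ceiling is 4652 × 4 = 18,608 visits. The real number is lower, because Trial status dates the end of recruitment to 11 September 2023 and only visits still to come count. The new questions cannot standardise visits already made, which is why step 3 is needed.

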### Frequency and plans for auditing trial conduct {23}

Fidelity to our trial procedures and interventions will be conducted weekly through the research assistant checklist (strategy and facility tracker) at 0, 12, and 24 months through an observation of training of treatment partners. Additionally, the data collection forms and modified EHR records will be audited at 0, 6, 12, 18, and 24 months for assessing treatment partner support and assessing required laboratory tests and anthropometry.

### Plans for communicating important protocol amendments to relevant parties (e.g., trial participants, ethical committees) {25}

Any changes to the protocol which may impact the conduct of the study or affect patient safety as well as any changes to the study objectives, design, patient population, sample sizes, study procedures, or significant administrative aspects will necessitate a formal amendment to the protocol. Such amendment will be agreed upon by the InterCARE team and NHLBI and approved by the UB IRB, DSMB, and the Botswana MoH HRDC prior to implementation and notified to the DHMTs.

### Dissemination plans {31a}

Our findings will be disseminated through presentations, reports, and publication in peer-reviewed journals and other publications. In-country data and country-specific information will be made available to national policy-makers and organizational and implementing partners. A detailed publication and communication plan will be developed that describes the number and types of reports and manuscripts planned for the study and criteria for authorship. Formal presentations at conferences and scientific publications will follow NIH, BHP, and MOH guidelines. The study results will be released to the participating health care workers, patients, and the general medical community.

## Discussion

While Botswana consistently reports an exemplary HIV care cascade [28], its escalating NCD burden presents a new challenge disproportionally affecting PLWH. Lessons learnt from HIV systems can be used to address the NCD burden, including HTN. The InterCARE study is the first implementation science hybrid type 2 cluster randomized clinical trial conducted in Botswana to address HIV NCD integration.

The InterCARE trial has some limitations which may limit generalizability. First, the clinics selected to participate in the trial have prior exposure to research principles. Second, although we distributed recruitment clinics geographically to cover most of the country, there are several remote areas where study set-up is not feasible with current resources.

In conclusion, the InterCARE trial has the potential to address the high burden of HTN in PLWH through integration into and leveraging well-established and successful HIV care program strategies in Botswana. The learning from InterCARE trial can inform integration of HTN and CVD risk management into HIV care more broadly in the region and globally.

## Trial status

Version 4. 27 November 2023. Recruitment began 31 January 2023 and completed 11 September 2023. Please note that the delay in submitting this protocol paper occurred due to the need to further adapt the implementation strategies from the pilot study (UG3) to the main trial (UH3).

## Data Availability

This study follows the NIH Public Access Policy, which ensures that the public has access to the published results of NIH funded research. All results will be made available from final peer-reviewed journal manuscripts via the digital archive PubMed Central upon acceptance for publication.

## Abbreviations

BP: Blood pressure
PWH: People with HIV
HIV: Human immunodeficiency virus
HTN: Hypertension
PWH and HTN: People with HIV and hypertension
CVD: Cardiovascular diseases
NCD: Non-communicable disease
ART: Antiretrovirals therapy
IDCC: Infectious Diseases Care Clinic
BCPP: Botswana HIV Combination Prevention Project
PIMS: Patient Information Management System
MoH: Ministry of Health
WHO: World Health Organization
UNAIDS: United Nations Program on HIV/AIDS
OPD: Outpatient department
HDFQ: Heart Disease Fact Questionnaire
REDCap: Research Electronic Data Capture
EHR: Electronic health records
CFIR: Consolidated Framework for Implementation Research
RE-AIM: Reach, Effectiveness, Adoption, Implementation, Maintenance
GLMM: Generalized linear mixed model
